#### Tertiary outcome measures

The frequency of post-traumatic stress symptoms will be assessed using the *Dutch version of the Impact of Event Scale (IES)* [62]*.* The IES is a 15-item self-report scale, measures the subjective stress following a traumatic event and is one of the most widely used self-report instruments of symptoms of post-traumatic stress [63]. It assesses three PTSD symptom subscales: (1) the intrusion (that is, the loss of voluntary control over the regulation of thoughts) subscale, (2) the avoidance (for example, the extent to which memories are consciously suppressed) subscale, and (3) the hyperarousal subscale. Items (for example, “pictures about it popped into my mind”) are rated on a four-point scale of frequency, ranging from “not at all” (0), “rarely” (1), “sometimes” (3), to “often” (5). The scores are summarized to produce a range of 0 to 75 for the total score. Patients will be explicitly instructed to fill out the IES related to the crucial traumatic memory that exacerbated or initiated their dental anxiety (M1). A score of 26 is considered the cut-off point for a clinically significant level of trauma-related symptomatology [64].

The fear of objects and situations related to the dental setting will be assessed using the *Fear of Stimuli Compromising the Dental Setting (FCDS) questionnaire.* This questionnaire includes the 25 most prevalent stimuli among 67 anxiety-provoking stimuli found in a study in 960 Dutch adults [1]. The fear provoking nature of each item will be scored on a four-point scale, from “not at all fear provoking” (1), to “extremely fear provoking” (4).

During the semi-structured interviews after the first and before the second dental extraction procedure, qualitative aspects of the memory for the recent dental extraction [M2] will be assessed (that is, vividness, emotional charge, avoidance and aversiveness propensity, sense of here and now, the impact of and burden caused by the memory). Patients will be asked to rate these characteristics on standardized continuous self-report VASs, ranging from 0 (for example, “not aversive at all”) to 100 (for example, “extremely aversive”).

The weeks after the dental extractions, the frequency and nature of intrusive thoughts will be indexed using an intrusions diary. Study participants will be asked to record their frequency and nature of their thoughts of the crucial traumatic event that exacerbated or initiated their dental anxiety (M1) for 7 days following the first and second dental extraction procedure.

A number of specific memory characteristics regarding the event that exacerbated or initiated their dental anxiety (M1) will be assessed using a 16-item self-report *Memory Characteristics Questionnaire (MCQ),* on two subscales; re-experiencing (eight items), disorganization (six items), peritraumatic dissociation (one item) and depersonalization and/or derealization during memory retrieval (one item) [65]. All 16 items are rated on a four-point scale ranging from “never” (0) to “all the time” (3).

The patients’ experiences during surgery will be assessed using visual analog scales (ranging from 0 to 100). Directly after the first and second (follow-up) dental extraction procedure, characteristics of participants’ experiences during surgery will be determined. Patients will be asked to rate the propensity of pain experienced during treatment, the degree of experienced reassurance/comforting by their surgeon, the sense of “here and now” when thinking back at this experience and how pleasurable the experience was. Patients will be asked to rate these characteristics on standardized continuous self-report VASs ranging from 0 (for example, “not reassured at all”) to 100 (for example, “completely reassured”).

#### Operative variables

A number of operative variables will be recorded by the surgeon after the first and second dental extraction procedure. These include the nature of the procedure (extraction/surgical removal; numbering of the dental elements extracted using the FDI World Dental Federation/ISO 3950:2009 notation), duration of the surgery, difficulty (that is, whether the surgery was experienced as a “complicated procedure”), number and location of anesthetic capsules administered, observer-rated anxiety (surgeons are asked to rate the question “according to you, how much anxiety did the patient show during treatment” using a continuous observer-rated VAS ranging from (0) “no anxiety at all” to (100) “extremely anxious”), nature of the follow-up treatment, and information on the occurrence of any adverse events.

#### Test of blindness

The patients’ blindness to treatment allocation will be assessed, with respect to the possibility of subsequent biased psychological or physical responses to the intervention. To this end, after all the study medication has been ingested following the first dental extraction, participants will be asked to answer the multiple-choice question “do you think that you have received: (a) the “real” capsules (with propranolol) or (b) the “fake capsules” (with placebo)” with either (a) or (b).

### Data management

To ensure data security and confidentiality, the coded anonymous case report forms will be stored in a locked room to which only the assessors have access.

### Statistical analysis plan

The distributions of demographic variables and quantitative data will be displayed in tables. Associations between categorical variables will be analyzed using the Chi^2^-test. Differences between the propranolol and placebo condition on continuous variables will be analyzed using the independent-samples t-test. Two-way (condition by time) repeated measures ANOVA will be used to compare the propranolol and placebo condition on the dental anxiety reduction between the first and second extraction, possibly with the baseline score as a covariate (if differences exist at baseline). The alpha is set at a significance level of 5 %.

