### Evidence for effects of propranolol on dental state anxiety

Currently one randomized, controlled clinical trial (RCT) evaluating the state anxiolytic effects of propranolol in dental phobia has been published. It showed that, as compared to placebo, 80 to 120 mg of oral propranolol significantly diminished self-reported state anxiety during injection of local dental anesthesia (self-reported anxiety about the injection: 5.5 (2.75) versus 7.45 (2.0), p = .033, one-tailed) [41]. A limitation to this study is that follow-up data were lacking. This means that to date, the long-term effects of propranolol on dental trait anxiety are unknown.

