### Study outcome measures

Dependent variables were derived from the questionnaires listed below (see Tables 1 and 2).

**Table 1 Tab1:** Primary and secondary study outcome measures

		Measures			
		Primary outcome	Secondary outcomes		
		Trait anxiety (S-DAI)	State anxiety (VAS score)	Vividness/emotional charge (M1) propensity (VAS scores)	Physiological response (HR/BP)
Screening (t = 0)	Screening interview				
Intervention (t = 1)	Preoperative interview	X		X	X
	Postoperative interview		X		
Follow-up (t = 2)	Preoperative interview	X		X	X
	Postoperative interview		X		

*Note:*
*BP* blood pressure, *HR* heart rate, *M1* crucial fear-related memory, *S-DAI* Short version of the Dental Anxiety Inventory, *VAS* visual analog scale

**Table 2 Tab2:** Tertiary outcome measures

		Measures							
		Operative variables/qualitative aspect of the surgical experience (VASs)	Test of blind	IES	FCDS	Qualitative aspect of memory M2 (VASs)	Qualitative aspect of memory M1 (VASs)	Intrusions diary	Specific phobia diagnosis
Screening (t = 0)	Screening interview				X				X
Intervention (t = 1)	Preoperative interview			X			X		
	Postoperative interview	X	X			X		X	
Follow-up (t = 2)	Preoperative interview			X	X	X	X		X
	Postoperative interview	X						X	

*Notes:*
*FCDS* fear of stimuli compromising the dental setting, *IES* Impact of Event Scale - Revised, *M1* crucial fear-related memory, *M2* memory of recent dental extraction procedure, *VAS* visual analog scale

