#### Secondary outcome measures

The self-reported state anxiety during dental treatment from baseline to 1-month follow-up will be indexed using a visual analog scale (Table 1). Patients are asked to rate the question “How much anxiety did you experience during the last treatment” using a standardized continuous self-report VAS ranging from “no anxiety at all” 0 to “extreme anxiety” 100.

Change from baseline to 1-month follow-up in self-reported vividness and emotional charge of the crucial fear-related memory will be measured using visual analog scales that assess key characteristics of the traumatic memory that initiated or exacerbated the dental anxiety (M1) (Table 1). Patients will be asked to rate the questions “how vivid or detailed is the memory, if you bring up the memory now” and “how much emotion does the memory evoke, if you bring up the memory now” using a continuous self-report VAS ranging from “no (anxiety/emotion) at all” (0) to “extremely much (anxiety/emotion)” (100).

Change from baseline to 1-month follow-up in physiological parameters during recall of the crucial fear-related memory (M1), will be assessed by bringing up the memory (M1) while the psychophysiological response (heart frequency per minute and blood pressure in mm Hg) will be indexed using an upper arm blood pressure measuring device (CE: 0297) (Table 1).

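### Patient-rated and surgeon-rated anxiety during surgery have no pre-dose score, and the plan adjusts them for no pre-dose measure, although a dental-fear score (FCDS) appears to be available

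*Protocol article*

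**What the plan says.** **Analysis.** The Statistical analysis plan section gives a general rule for continuous variables: "Differences between the propranolol and placebo condition on continuous variables will be analyzed using the independent-samples t-test". It names no outcome. The next sentence turns to change over time: "repeated measures ANOVA will be used to compare the propranolol and placebo condition on the dental anxiety reduction between the first and second extraction". For adjustment, that analysis has a single provision, which depends on the data: "possibly with the baseline score as a covariate (if differences exist at baseline". That conditional baseline score is the only covariate in the section. The Sample size calculation section ties this ANOVA to the primary outcome, the S-DAI.

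**Outcomes first rated after dosing.** Patients rate state anxiety on a 0 to 100 VAS with the question "How much anxiety did you experience during the last treatment" (Secondary outcome measures). Table 1 places this rating only at the postoperative interviews of t = 1 and t = 2. Surgeons rate "according to you, how much anxiety did the patient show during treatment" after each procedure (Operative variables). The Secondary aims nevertheless describe state anxiety as a change from baseline to four weeks.

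**The available fear score.** Table 2 lists the FCDS ("fear of stimuli compromising the dental setting") at the t = 0 screening interview and again before the second extraction. It has 25 items scored 1 to 4, and the Tertiary outcome measures section introduces it with "The fear of objects and situations related to the dental setting will be assessed using the". The article uses it only as a tertiary outcome.

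**The concern.** Reducing anxiety during surgery is one of the three treatment targets in the rationale, and the Active substance section gives it as the purpose of the preoperative dose. With about 17 patients per arm, an unadjusted comparison leaves all between-patient variation in dental fear in the error term. Any chance difference in fear between the arms also carries into the estimated effect. A fear score measured before dosing could reduce both problems without new data.

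The ANOVA reading does not supply such a score. The first state-anxiety rating is made under study medication and the second without it. Using the first as the baseline covariate would adjust for a value that the drug may already have changed, and so could remove part of the effect of interest.

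**Working it through.** **1. Timetable.** Table 1 has no state-anxiety entry before the first postoperative interview. Table 2 puts the FCDS and the specific phobia diagnosis in the same t = 0 row. The First preoperative assessment section describes the phobia diagnosis, and the Treatment allocation section places randomisation after that interview. The t = 0 FCDS is therefore probably obtained before dosing. This is an inference: the First preoperative assessment section does not name the FCDS, and the First dental extraction procedure section also uses the word screening for a session after ingestion.

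**2. The plan's own sample size.** For the condition-by-time interaction, λ = f² × N × m / (1 − ρ) = 0.25² × 34 × 2 / (1 − 0.50) = 8.5, with 1 and 32 degrees of freedom. Power is 80.7% at N = 34 and 78.1% at N = 32, so the stated 34 is reproduced. It applies to the S-DAI only.

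**3. Illustrative effect.** The Background cites an earlier trial of anxiety about a dental injection: "5.5 (2.75) versus 7.45 (2.0), p = .033, one-tailed". If the brackets are standard deviations (an assumption), the pooled SD is √((2.75² + 2.0²)/2) = 2.404 and d = (7.45 − 5.5)/2.404 = 0.81.

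**4. Unadjusted power.** With 17 per arm and a two-sided 5% level (the article does not state sidedness), the noncentrality is 0.811 × √(17/2) = 2.36 with 32 degrees of freedom. Power is 63.0%.

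**5. Adjusted power.** With one covariate correlated r with the outcome, the residual variance is multiplied by 1 − r². The noncentrality is d/√(1 − r²) × √(17/2) × √(30/31) with 31 degrees of freedom; the last factor is an approximate allowance for chance imbalance in the covariate. At r = 0.5 this is 0.811/0.866 × 2.915 × 0.984 = 2.69. The values of r are assumptions.

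| r | Residual variance | Power at d = 0.81 | Power at d = 0.5 |
|---|---|---|---|
| t-test | 1.00 | 63.0% | 29.3% |
| 0 | 1.00 | 61.5% | 28.5% |
| 0.2 | 0.96 | 63.3% | 29.4% |
| 0.3 | 0.91 | 65.6% | 30.8% |
| 0.5 | 0.75 | 74.0% | 36.1% |

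The difference detectable with 80% power is 0.99 SD unadjusted, 0.96 SD at r = 0.3 and 0.87 SD at r = 0.5. A simulation of 4,000 trials per setting agreed: adjusted power at d = 0.81 was 62.6%, 65.4% and 73.1% at r = 0, 0.3 and 0.5.

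**6. Chance imbalance.** The standard error of the between-arm difference in a baseline score is √(2/17) = 0.34 SD. The chance of a difference beyond 0.5 SD in either direction is about 14%. At r = 0.5, such a difference moves the unadjusted result by 0.5 × 0.5 = 0.25 SD.

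**7. Validity.** With no treatment effect, and r = 0, 0.3, 0.5 and 0.7, the simulated type I error was 4.6% to 5.5% for the t-test and 4.9% to 5.2% for the adjusted model.

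**The case against.** The strongest reply is that nothing here is an error. Randomisation makes the unadjusted t-test unbiased on average, and its type I error is close to 5%. The outcomes concerned are secondary or lower, and a separate analysis plan may name covariates. This stands as far as validity goes. It does not remove the point, because the article does fix a method and a covariate rule, and that rule gives these outcomes no pre-dose covariate.

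A reader might infer that the plan expressly assigns state anxiety to the t-test. It does not. The t-test sentence is generic and may refer to group comparisons in general, and the ANOVA sentence could be read to include state anxiety, which is rated after exactly those two extractions. The sample size section makes the t-test reading plausible, not certain. Under either reading no pre-dose covariate is specified.

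A reader might also infer that power is certainly lost. The documents give no correlation between the FCDS and state anxiety. Entry is limited to scores 3 and 4 on the four-point fear question, which may lower that correlation, and the FCDS covers dental stimuli in general. At r of about 0.2 or less there is no gain. The illustrative d also comes from a different endpoint.

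Finally, it is tempting to require FCDS adjustment for every outcome first rated after dosing. The documents do not support the FCDS as a predictor of pain, the other experience ratings, M2 ratings or diary frequency.

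**Conclusion.** The point holds as one of efficiency and conditional imbalance, not of bias or invalidity. It concerns the state-anxiety VAS and surgeon-rated anxiety, and leaves the primary outcome untouched. The stated analysis is valid but probably not the best use of about 34 patients. At d = 0.81, adjustment changes power from 63% to between about 62% (r = 0) and 74% (r = 0.5).

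This rests on five assumptions: 17 analysed per arm, a two-sided test, brackets in the cited trial that are standard deviations, a value of r that the document does not give, and a t = 0 FCDS completed before the first capsules. The last can be settled by the sponsor. Because the possible loss is small and the possible gain is several times larger, the change is worth making.

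**What to change.** First confirm, and state in the article's timetable, that the t = 0 FCDS is completed before the first capsules. Then amend the Statistical analysis plan section along these lines: *The state-anxiety VAS at each extraction and surgeon-rated anxiety will be compared between conditions with a linear model containing condition and the t = 0 FCDS total score. The covariate is prespecified and will be included whether or not the arms differ at baseline. The first state-anxiety rating, made after dosing, will not be used as a baseline covariate. An unadjusted t-test will be reported as a supportive analysis.*

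Adjustment of pain, the other surgical-experience ratings, M2 ratings and diary frequency is optional.

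The cost is a short amendment before unblinding and one degree of freedom, with no new data. If the FCDS is unrelated to the outcome, power falls by about 1.5 points (63.0% to 61.5% at d = 0.81).

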### Secondary aims

The secondary aims are to determine whether the use of propranolol in patients with high self-reported levels of fear in anticipation of tooth or molar removal results in the following:a significantly greater reduction of self-reported intraoperative (state) anxiety, compared to the placebo comparator, from baseline to the 4-week follow-up appointment;a significantly greater decrease of physiological responding during recall of the crucial fear-related memory, compared to the placebo comparator, from baseline to the 4-week follow-up appointment;a significantly greater decrease in specific phobia diagnoses, compared to the placebo comparator, from baseline to the 4-week follow-up appointment;a significantly greater reduction of self-reported vividness and emotional charge of the crucial fear-related memory scores, compared to the placebo comparator, from the baseline to the 4-week follow-up appointment.

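### The t-test named for continuous variables does not say which value it compares, and no baseline-adjusted analysis is named for M1 vividness, M1 emotional charge, heart rate and blood pressure

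*Protocol article*

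**What the plan says.** Three parts of the protocol article bear on this.

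- **Aims and outcome definitions.** Secondary aims asks for "a significantly greater decrease of physiological responding during recall of the crucial fear-related memory" and for "a significantly greater reduction of self-reported vividness and emotional charge of the crucial fear-related memory scores", each against placebo and from baseline to 4 weeks. Secondary outcome measures defines the outcomes the same way, for example "Change from baseline to 1-month follow-up in physiological parameters during recall of the crucial fear-related memory (M1"). Table 1 marks all four measures at the preoperative interview of both t=1 and t=2.
- **Analysis.** The Statistical analysis plan section states "Differences between the propranolol and placebo condition on continuous variables will be analyzed using the independent-samples t-test". It then says "Two-way (condition by time) repeated measures ANOVA will be used to compare the propranolol and placebo condition on the dental anxiety reduction" between the two extractions, "possibly with the baseline score as a covariate (if differences exist at baseline"). The longitudinal model and the covariate both belong to that one sentence about dental anxiety.
- **Baseline timing.** First preoperative assessment describes an interview before medication. It lists M1 ratings such as avoidance, aversiveness, impact and burden, but not vividness, emotional charge, heart rate or blood pressure. First dental extraction procedure places a 30-minute investigator screening, which refers the reader to the outcome measures, between ingestion and surgery.

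**The concern.** The four M1 outcomes carry the trial's claim about memory reconsolidation, and they are to be compared in 34 patients. The one stated test that can cover them leaves open which number goes into it. On follow-up values, the test leaves a collected baseline unused and compares something other than the change named in the aims. On change scores, it matches the aims but subtracts the whole baseline difference, which over-corrects a chance imbalance whenever the correlation between visits is below 1. The two versions can give clearly different estimates from the same data, so the choice should not be left until the data are seen. Both use the baseline less efficiently than a model that includes it as a covariate.

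Self-reported state anxiety is left out of this point, because its first rating follows the medicated procedure and so is not an untreated baseline.

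**Working it through.** **1. The plan's own figure.** Inputs from Sample size calculation: f = 0.25, correlation 0.50, alpha 0.05, power 0.80, two groups, two measurements. For the condition-by-time interaction, lambda = f² × N × 2 / (1 − r).
- N = 34: 0.0625 × 34 × 2 / 0.50 = 8.5, with 1 and 32 df, power 0.807.
- N = 32: power 0.781. The stated 34 reproduces.
- The square root of 8.5 is 2.915. A t-test on change has noncentrality d / √(2(1 − r) × 2/17), which at r = 0.50 is d / 0.343. So d = 1.0 SD is the effect the plan assumes for the S-DAI.

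**2. Is a t-test on change a different test from the interaction?** No. With two groups and two visits they are identical. On a simulated 17 + 17 data set, t² = 12.429 and F(1, 32) = 12.429, both with p = 0.0013.

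**3. Power of the three candidate analyses.** Assumptions: 17 v 17, two-sided 5%, equal variances, pre-dose baseline. The documents give no SD, correlation or effect for these outcomes, so 0.8 SD and the correlations are assumptions; 0.50 is borrowed from the S-DAI. Noncentrality = d / √(V × 2/17), with √(2/17) = 0.343 and:
- follow-up t-test: V = 1, 32 df;
- change-score t-test: V = 2(1 − r), 32 df;
- ANCOVA: V = (1 − r²) × 31/30, 31 df. The factor 1 + 1/30 allows for chance baseline imbalance.

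Worked at r = 0.50 and d = 0.8:
- Either t-test: V = 1, noncentrality 0.8 / 0.343 = 2.33, power 0.62.
- ANCOVA: V = 0.75 × 31/30 = 0.775, noncentrality 0.8 / (0.343 × 0.880) = 2.65, power 0.73.

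| r | Follow-up t-test | Change t-test | ANCOVA |
|---|---|---|---|
| 0.30 | 0.62 | 0.48 | 0.64 |
| 0.50 | 0.62 | 0.62 | 0.73 |
| 0.70 | 0.62 | 0.83 | 0.88 |

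The difference detectable with 80% power at r = 0.50 is 0.99 SD for either t-test and 0.87 SD for ANCOVA. At r = 0.70 it is 0.99 (follow-up), 0.77 (change) and 0.72 SD (ANCOVA). At the plan's own 1.0 SD and r = 0.50, power is 0.81 for either t-test and 0.89 for ANCOVA (0.90 without the small-sample factor).

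**4. Effect of chance imbalance.** One standard error of the baseline difference is √(2/17) = 0.34 SD. It shifts the follow-up estimate by r × 0.34 and the change estimate by (r − 1) × 0.34.
- r = 0.50: +0.17 and −0.17 SD.
- r = 0.70: +0.24 and −0.10 SD.

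The gap between the two estimates is always the full baseline difference, here 0.34 SD.

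**The case against.** **The test fits the aim.** A reader might infer that the stated t-test cannot test a greater decrease from baseline. The documents do not support that. Secondary outcome measures defines these outcomes as change, so a t-test on change is a natural reading, and step 2 shows it is the same test as the interaction. This stands.

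**Validity is intact.** Under randomisation with an untreated baseline, both t-tests and ANCOVA are unbiased with correct type I error, and the standard error already allows for chance imbalance. This also stands. The loss is of precision, plus the unfixed choice of value.

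**The sentence may be descriptive.** It follows one on tabulating distributions and a generic one on categorical variables, and the article condenses a fuller document. That is possible. But the section is headed as the analysis plan and names a test for continuous variables. The point is that the stated choice is loosely fixed, not that detail is absent.

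**The inputs are borrowed.** The correlation of 0.50 belongs to the S-DAI and 0.8 SD appears nowhere in the article. This is correct, which is why a range is shown. ANCOVA has the highest power at each correlation in it, though at 0.30 its gain over the follow-up test is only 0.02.

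**A pre-dose baseline is not established.** A reader might also infer that ANCOVA can simply be written in. It cannot yet. If heart rate, blood pressure or the M1 ratings at t=1 are taken after ingestion, propranolol may already have altered them. Adjusting for such a value, or subtracting it, could bias the comparison. The follow-up t-test would then be the one version of the three not affected. This objection stands and conditions the fix.

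**Conclusion.** The point holds as one of precision and specification, not of validity. The article does not say which value the t-test compares and names no baseline-adjusted analysis for the four M1 outcomes, although it defines them as change and measures them twice. ANCOVA would raise power at an assumed 0.8 SD from 0.62 to 0.73 at a correlation of 0.50. At 0.30, choosing one t-test over the other moves power between 0.62 and 0.48, more than ANCOVA adds to the better of them (0.64). These figures rest on 17 analysed patients per arm, equal variances, assumed effects and correlations, and a baseline taken before ingestion. The article leaves that last condition unclear, so the case for adjustment is conditional on it, outcome by outcome.

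**What to change.** 1. Reconcile First preoperative assessment, Treatment allocation, First dental extraction procedure and Table 1. State for each of M1 vividness, M1 emotional charge, heart rate and blood pressure whether the t=1 value is recorded before or after ingestion of study medication.
2. For each outcome confirmed as pre-dose, state in the Statistical analysis plan section that the follow-up value is compared between arms by ANCOVA, with that outcome's own baseline always included whatever the observed baseline difference. Report the adjusted mean difference with its 95% CI.
3. For any outcome whose t=1 value is post-dose, do not use that value as a covariate or in a change score. Compare the follow-up values between arms and say so.
4. Reserve the independent-samples t-test for variables with a single usable measurement.

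The cost is a short edit before unblinding and one degree of freedom per ANCOVA model. No extra patients are needed. Where a t=1 value proves to be post-dose, the precision gain is not available for that outcome.

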### Sample size calculation

A power analysis was performed for the primary outcome variable, dental trait anxiety as indexed by the Short-version of the Dental Anxiety Inventory (S-DAI). In order to detect a difference between the propranolol and control condition on changes in dental anxiety scores over time, a two-way (one-within and one-between subjects factor) repeated measures ANOVA will be used. Using G*Power 3.0 software, assuming a correlation of 0.50 between two repeated measurements, a medium size treatment effect (f = 0.25), a power of 0.80, an α significance level of 0.05, and two treatment conditions, the power analysis results in a total sample size of 34 persons.

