#### Primary outcome measure

The primary aim is to assess the reduction in the dental trait anxiety score in the propranolol versus the placebo control group (Table 1). The change from baseline to 1-month follow-up in dental trait anxiety will be indexed with the Dutch version of the *Short version of the Dental Anxiety Inventory* (S-DAI) [60]. The items (for example, “when I know the dentist/oral-maxillofacial surgeon is going to extract a tooth, I am already afraid in the waiting room”) are answered on a five-point Likert-type scale, ranging from “totally not applicable to me” (1) to “totally applicable to me” (5). Total scores on this questionnaire range from 9 to 45. The clinical cut-off score for a patient to apply for treatment in a specialized dental fear clinic is a minimum of 28 points on the S-DAI [61].

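### Baseline S-DAI enters the primary model only if arms appear to differ, with no criterion: precision is lost, unflagged imbalance is over-corrected, and the model is not fixed

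*Protocol article*

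**What the plan says.** The Statistical analysis plan section of the protocol article names the primary model: "Two-way (condition by time) repeated measures ANOVA will be used to compare the propranolol and placebo condition on the dental anxiety reduction". The two time points are the two surgical visits, four weeks apart. The section then adds the baseline score only conditionally: "possibly with the baseline score as a covariate (if differences exist at baseline". The section does not say how a difference is to be judged, and the first word of that clause leaves the choice open even when a difference is found. The same section assigns t-tests to continuous variables in general ("Differences between the propranolol and placebo condition on continuous variables will be analyzed using the independent-samples t-test") but does not link them to the covariate decision.

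The Sample size calculation section uses the unadjusted model: "a two-way (one-within and one-between subjects factor) repeated measures ANOVA will be used", "assuming a correlation of 0.50 between two repeated measurements", with "a medium size treatment effect (f = 0.25), a power of 0.80, an α significance level of 0.05, and two treatment conditions", giving 34 participants in total. The Primary outcome measure section defines the endpoint as a change score: "The change from baseline to 1-month follow-up in dental trait anxiety will be indexed with the Dutch version" of the S-DAI. No other section settles the covariate.

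**The concern.** Allocation is random, so a difference between arms in a pre-dose baseline score is chance. A covariate's value depends on how well it predicts the outcome, not on whether the arms happen to differ on it. Waiting for an observed difference means that most trials would be analysed without a covariate that the design itself assumes to correlate 0.50 with the outcome.

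Three things are at stake:

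- **Precision.** The score is already collected, but its information is mostly unused.
- **Conditional bias.** An imbalance too small to be flagged, but not small in effect, distorts the change-score estimate.
- **A fixed primary model.** Two analysts following the text could fit different models to the same data, and with 34 patients the choice can decide significance.

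**Working it through.** **Inputs.** From the article: N = 34, allocation 1:1 (17 per arm), r = 0.50, f = 0.25, α = 0.05. Assumed: bivariate normal scores, equal SDs, no dropout, a two-sided baseline t-test as trigger (p<0.05, 0.10 or 0.20), and r from 0.3 to 0.7 as the range around 0.50. The article gives no S-DAI standard deviation, so results are in SD units.

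**1. The plan's own figure.** For the within-between interaction with m = 2 measurements, λ = N·m·f²/(1−r) = 34 × 2 × 0.0625/0.5 = 8.5, on 1 and 32 df. Power is 0.807 at N = 34 and 0.781 at N = 32. The stated 34 is reproduced, without any covariate.

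**2. What that effect means.** In a 2×2 interaction, f = 0.25 is a between-arm difference in change of 4f = 1.0 SD. The SD of change is √(2(1−r)) = 1.0 SD at r = 0.50. The t-test on change therefore has non-centrality 1.0 × √(34/4) = 2.915, whose square is 8.5. The two analyses are the same test.

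**3. ANCOVA at the same N.** The residual SD is √(1−r²) = 0.866. The variance ratio to the change score is (1−r²)/(2(1−r)) = (1+r)/2 = 0.75. With allowance for random imbalance, non-centrality is (1/0.866) × √(34/4 × 30/31) = 3.31 on 31 df, and power is 0.894. About 28 patients would reach 80% (0.820 at N = 28, 0.787 at N = 26).

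**4. The conditional rule.** This was simulated with 400,000 trials per scenario: ANCOVA if the baseline test is below the trigger, otherwise the change score.

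| r | Unadjusted | Rule, p<0.05 | Always ANCOVA |
|---|---|---|---|
| 0.3 | 66.6% | 67.6% | 82.9% |
| 0.5 | 80.6% | 81.3% | 89.3% |
| 0.7 | 95.5% | 95.7% | 97.3% |

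At r = 0.50 the rule gives 82.0% with a p<0.10 trigger and 83.1% with p<0.20. It keeps about 8%, 16% and 29% of the available gain at the three triggers.

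**5. Overall type I error.** With the p<0.05 trigger it is 4.1%, 4.3% and 4.6% at r = 0.3, 0.5 and 0.7.

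**6. Unflagged imbalance.** The SD of the chance baseline difference is √(2/17) = 0.343 SD. The 5% trigger is reached only near 2.04 × 0.343 = 0.70 SD. The share of trials with an imbalance above 0.4 SD that stays non-significant is about P(|Z| > 0.4/0.343) − 0.05 = 0.244 − 0.05 = 0.19. The change score subtracts the baseline difference with slope 1 where slope r is correct, which leaves a bias of (1−r) times the imbalance. The mean imbalance in that subset is about 0.515 SD, so the bias is 0.5 × 0.515 = 0.26 SD. It favours propranolol when that arm starts higher and placebo when it starts lower, each in about half of the subset. Type I error within the subset is about 8% for the change score and about 5% for ANCOVA.

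**7. Cost of discretion.** If either model may be reported, the chance under no effect that at least one is significant is about 7.3% at r = 0.50 (7.8% at r = 0.3, 6.8% at r = 0.7). At the planned effect and r = 0.50, the two models disagree on significance in about 12% of trials.

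**The case against.** The strongest reply is that nothing promised is lost. The trial was sized on the unadjusted ANOVA, and that analysis delivers 80.7% power at 34 patients. This stands: a reader might infer that the trial is underpowered, and the article's own figures do not support that.

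A reader might also infer that the rule inflates the false-positive rate. Under a fixed trigger it does not; overall error is slightly below 5%. The 8% applies only to a selected subset, and the 7.3% is an upper bound for unrestricted choice between two models, which the article does not say will be exercised.

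Nor is it right that chance imbalance goes uncorrected. The change score removes too much of it, and a flagged imbalance may be adjusted by the covariate.

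The Blinding section says that the statistician is blinded, and the covariate decision uses baseline data, so nothing ties the choice to unblinded results. This limits deliberate choice by arm. It does not remove the dependence on the data, the conditional bias or the lost power.

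Finally, an article may leave a threshold to a separate analysis plan. That is fair for the threshold, but the conditional principle is stated here, and defining the threshold would not cure it.

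One objection limits the remedy. ANCOVA is sound only if the baseline precedes treatment. First preoperative assessment places questionnaires before ingestion of study medication. First dental extraction procedure places a 30-minute screening, cross-referenced to the outcome measures, between ingestion and surgery. Table 1 lists the first S-DAI, M1 memory ratings and heart rate/blood pressure at the intervention-day preoperative interview without saying which side of dosing that is. If a first reading is taken after a beta-blocker, a difference between arms is no longer pure chance, and neither ANCOVA nor the change score is then clean.

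**Conclusion.** The concern holds as an efficiency and pre-specification defect in the primary analysis, worth correcting but not fatal. At the article's r = 0.50, always adjusting raises power from about 81% to 89%, and the conditional rule forgoes about 71% to 92% of that gain for triggers from p<0.20 to p<0.05. The direction is the same at r = 0.3 and 0.7, with a much smaller absolute gain at 0.7. In about one trial in five, an unflagged imbalance shifts the estimate by about 0.26 SD, in either direction.

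Planned power is met and overall type I error is not inflated under a fixed trigger. The figures for the conditional rule rest on the assumed baseline t-test trigger, because the article names none. All figures rest on normality, equal SDs and no dropout. The case for ANCOVA also requires a pre-dose baseline S-DAI, which the article leaves ambiguous.

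**What to change.** Delete the bracketed condition and the word that makes adjustment optional. Suggested text: *The primary analysis is an ANCOVA of the 4-week S-DAI on treatment, with pre-dose baseline S-DAI as covariate, fitted regardless of observed baseline balance. The repeated measures ANOVA is a sensitivity analysis.*

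Reconcile First preoperative assessment, First dental extraction procedure and Table 1, so that the text states whether each first measurement precedes ingestion of study medication. Apply the same model to the M1 vividness and emotional charge ratings and to heart rate/blood pressure only where their baseline is confirmed as pre-dose.

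The cost is a sentence or two in the analysis text and a clarification of timing, made before unblinding. The S-DAI is already collected and the article reports the trial as still recruiting, so no extra patients or visits are needed.
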